## Abstract

**Background:**

Rotator cuff tears are the most common source of shoulder pain and disability. Only poor quality studies have compared mini-open to arthroscopic repair, leaving surgeons with inadequate evidence to support optimal, minimally-invasive repair.

**Methods/Design:**

This randomized, multi-centre, national trial will determine whether an arthroscopic or mini-open repair provides better quality of life for patients with small or moderate-sized rotator cuff tears. A national consensus meeting of investigators in the Joint Orthopaedic Initiative for National Trials of the Shoulder (JOINTS Canada) identified this question as the top priority for shoulder surgeons across Canada. The primary outcome measure is a valid quality-of-life scale (Western Ontario Rotator Cuff (WORC)) that addresses 5 domains of health affected by rotator cuff disease. Secondary outcomes will assess rotator cuff functionality (ROM, strength, Constant score), secondary dimensions of health (general health status (SF-12) and work limitations), and repair integrity (MRI). Outcomes are measured at baseline, at 6 weeks, 3, 6, 12, and 24 months post-operatively by blinded research assistants and musculoskeletal radiologists. Patients (n = 250) with small or medium-sized cuff tears identified by clinical examination and MRI who meet eligibility criteria will be recruited. This sample size will provide 80% power to statistically detect  a clinically important difference of 20% in WORC scores between procedures after controlling for baseline WORC score (α = 0.05). A central methods centre will manage randomization, data management, and monitoring under supervision of experienced epidemiologists. Surgeons will participate in either conventional or expertise-based designs according to defined criteria to avoid biases from differential surgeon expertise. Mini-open or all-arthroscopic repair procedures will be performed according to a standardized protocol. Central Adjudication (of cases), Trial Oversight and Safety Committees will monitor trial conduct. We will use an analysis of covariance (ANCOVA), where the baseline WORC score is used as a covariate, to compare the quality of life (WORC score) at 2 years post-operatively. As a secondary analysis, we will conduct the same statistical test but will include age and tear size as covariates with the baseline score. Enrollment will require 2 years and follow-up an additional 2 years. The trial will commence when funding is in place.

**Discussion:**

These results will have immediate impact on the practice behaviors of practicing surgeons and surgical trainees at JOINTS centres across Canada. JOINTS Canada is actively engaged in knowledge exchange and will publish and present findings internationally to facilitate wider application. This trial will establish definitive evidence on this question at an international level.

## Background

### Rotator cuff is essential to function, but at risk of injury

The shoulder joint is essential for placing the hand in functional positions and as such requires mobility, strength, and stability. To provide mobility, the joint has a small shallow glenoid upon which the humeral head is permitted a large range of movement. Unlike other socket joints like the hip where bony structure provides stability, in the shoulder, stability is provided primarily by muscles. This defines the critical importance of the rotator cuff muscles and the cascade of events that follow when cuff integrity is compromised. The rotator cuff muscles are responsible for dynamic stabilization of the glenohumeral joint during shoulder motion. During abduction, the supraspinatus and the deltoid muscle work synergistically to elevate the arm. The infraspinatus, subscapularis, and teres minor depress the humeral head and maintain joint stability by opposing the upward forces created by the supraspinatus and deltoid. A cuff tear can occur after a single extreme overload, but typically it is the result of a degenerative process that compromises tendon integrity, starting with supraspinatus [1] and progressing to the other cuff muscles. A rotator cuff tear destroys the balance of forces at the shoulder and as a result, the humeral head is driven superiorly, resulting in pain, loss of strength, and reduced motion – all of which contribute to a profound functional loss. The progression of a complete cuff tear leads to rotator cuff arthropathy (osteoarthritis).

### There is a high incidence of tears

It has been established that degeneration, i.e., frictional wear in the presence of hypovascularity, is the primary mechanism of rotator cuff tears [1-4] with anatomic factors, i.e., acromial shape, having a smaller or uncertain role [5,6]. Thus, aging and overuse both contribute to high rates of cuff pathology. There is consensus across epidemiological studies that full thickness tears increase with age [1-3,7-9], with some studies reporting an incidence of 5% in patients in their fourth decade and 80% of those in their eighth decade [1-3,5,7,10]. While rates vary across studies, there is consensus that incidence is high and that changes are often bilateral and age dependent.

### A cuff tear has a large effect on disability and quality of life

The impact of rotator cuff pathology on overall health, work productivity, and quality of life is profound. A study of over 500 shoulder problems, including 111 rotator cuff tears, indicated that health status was equally compromised in these patients as compared to 5 major medical diagnoses (hypertension, congestive heart failure, acute myocardial infarction, diabetes mellitus, and clinical depression) [11]. Others have confirmed the impact of cuff disease on health at the primary care level [12]. A substantial loss in work productivity is evident in the high claims rates and costs attributed to cuff disease in the worker's compensation system [9,13,14], where cuff pathology ranks second to back pain as a reason for lost time from work in manual workers [14]. Cuff pathology results in high levels of pain, disability, and reduced quality of life compared to age-matched controls [15]. It has been shown that the presence of cuff pathology is a primary determinant of health status (SF-36) (R^2 ^= 72%) [15]. Furthermore, rotator cuff surgery has been shown to have a significant impact; not just on shoulder symptoms, but also on overall health status [16].

### Studies on arthroscopic and mini-open repairs are low quality and inconclusive

There has been a move across surgical disciplines to minimize the extent of surgical dissection required to perform procedures. Procedures that have traditionally been performed though open techniques are now performed arthroscopically or through mini-open procedures. For example, there have been sufficient numbers of randomized controlled trials (RCTs) comparing open and endoscopic carpal tunnel release that systematic reviews have now been completed on this topic [17]. Recently, both arthroscopic and mini-open procedures have been introduced into shoulder surgery. While both interventions are less invasive than open procedures, there are variable advantages and concerns with these two procedures [18]. Repair by an all-arthroscopic procedure is less invasive, but requires more extensive training [18]. While a more rapid recovery might be expected, the adequacy of the repair and risk of complications have been questioned [19]. Some surgeons are reluctant to invest time in training for this procedure, unless it can be shown that an all-arthroscopic repair provides superior results [18,20].

A few low-quality (level 4) case series have evaluated the outcomes of these two surgical interventions. A completely arthroscopic technique has been reported as effective across a spectrum of tears [21-28], specifically in small to medium [21], moderate to large [29], and large/massive tears [19]. There is consensus across these studies that clinical improvements can be obtained in the majority of cases, although a recurrent defect was reported in 17/18 large or massive tears [19]. Similarly, other cases series report a high percentage of good/excellent results in patients treated with arthroscopically assisted mini-open repairs across a spectrum of tear sizes, specifically for both small/moderate to large [30] tears.

Three low-quality (level 3) studies have reported head-to-head comparison of mini-open versus all-arthroscopic rotator cuff repair [31-33]. Two studies (n = 19 [32] and n = 76 [33]) found similar disability and strength scores at follow-up; another study [31] reported similar long-term disability, but faster return of motion in the arthroscopic group as compared to the mini-open procedure. In these studies [31-33], patients were not randomized, follow-up was retrospective, and in one study [33], patients received a mini-open procedure following "technical failure" of arthroscopic repair. Thus, these low-quality studies from different subpopulations may be biased since groups potentially differ in their prognostic balance. Further, comparison across previous studies is difficult due to variation in patient selection techniques, symptom duration, disability levels, and extent of pathology. To date, no randomized clinical trial has attempted to compare the results of an all-arthroscopic repair to an arthroscopically assisted mini-open repair. High-quality evidence is required to assist surgeons to determine whether the move towards less invasive procedures in cuff repair is appropriate.

### There are challenges in conducting surgical trials in orthopaedic surgery

There are a number of barriers to the conduct of randomized clinical trials in surgical practices. One such barrier is the influence of surgeon skill as a component of the treatment process [34]. Surgeons are rarely equally competent at two different surgical procedures for the same clinical problem, and even more rarely do they believe that two surgical options are equally beneficial [34]. Thus, the classic randomized trial developed in medicine to evaluate drug therapies can fall short when applied to the evaluation of surgical interventions, where skill and preference for a particular procedure have the potential to bias the results or challenge the feasibility of the trial. In fact, it has been shown that surgeons are less likely to participate in Randomized Controlled Trials (RCTs) as compared to other medical specialties [35]. Surgeons may be reluctant to participate in trials because they do not consider themselves to be in a position of equipoise or may be reluctant to enroll all patients because of treatment preferences. High-quality trials require a broad level of participation to achieve the sample sizes required for adequate power.

To address these challenges, shoulder surgeons across Canada formed a national collaborative group focused on multi-centered clinical trials for shoulder conditions (Joint Orthopaedic Initiative for National Trials of the Shoulder) (JOINTS Canada). Most recently, JOINTS Canada obtained CIHR funding to complete strategic planning on the priority research question facing shoulder surgeons and to identify trial methods suited to meet the challenges inherent in surgical trials.

### Expertise-based random allocation may enhance feasibility and validity

In 1980, randomizing subjects to clinicians was first suggested by Van der Linden [36,37]. Since that time, however, this design has been little used. The expertise-based randomized controlled trial has been recently revisited as a potential alternative to minimizing these barriers [34]. In a conventional RCT, both interventions are offered by each health care provider. This works well in drug trials where there is no interaction between the drug and its provider and where the provider can be blinded to the intervention they are dispensing. However, in surgical trials there are problems with this approach that have been recently described by the Expertise-Based Group [34]. The primary concern is that the conventional RCT may actually introduce a bias, due to "differential expertise" within a treatment group that may act as a confounder leading to spurious or biased results. It has been well established that the patients of surgeons who have more experience can expect better outcomes following a surgical intervention. Thus, the patients of surgeons participating in a conventional clinical trial will tend to have better outcomes if they are assigned to the treatment in which their surgeon is more experienced. Greater imbalance in expertise between surgeons compounded by an imbalance in recruitment rates between surgeons will result in greater differential expertise bias and lower trial validity. In fact, extensive experience may be required to achieve superior outcomes. Thus, conducting a specific number of "run-in cases" prior to enrolling patients (used in conventional RCTs) does little to impact on this form of bias.

Not only do surgeons have differential expertise, but also this is often associated with strong beliefs about which intervention is more effective. In fact, initial beliefs of trial surgeons about which intervention is superior has been shown to persist at the end of the trial [34]. Therefore, it is possible that surgeons will introduce differential treatment bias by managing cases with their preferred intervention in a more rigorous manner. Although self-report measures can obviate the impact of surgeon bias on measurement of outcomes, these cannot control for differential treatment bias. Another form of bias tends to manifest itself in the conventional design because a greater number of procedural crossovers (surgeon does not comply with the random assignment) occur when the patient is assigned to the less preferred treatment arm. Increased rates of crossing over also compromise the validity of the RCT results. Finally, from an ethical viewpoint, it is preferable that patients receive care from a surgeon using a procedure that they were experienced in performing.

Despite these potential advantages, the expertise-based design has rarely been used except in cases where the interventions arise from different disciplines [34]. After consulting with experts [34], we devised a strategy to maximize valid participation of trial surgeons. Given the potential for differential expertise bias, we concluded that only surgeons with long-term (>2 years) and recent experience in both procedures were appropriate for the conventional RCT in our study. Those who demonstrated differential expertise or preference are required to participate in the expertise-based RCT. While this requires two designs, it ensures that the potential bias due to differential expertise or preference for one procedure over another is reduced.

### Systematic reviews confirm that treatment is based on inadequate evidence

Two separate research teams have attempted to conduct systematic reviews to summarize the available evidence for management of shoulder problems, including rotator cuff disease. A 1998 systematic review included all randomized trials that addressed shoulder pain and any related treatment intervention and found insufficient evidence to make any specific recommendations with regards to management of rotator cuff disease [38]. A recent systematic review of surgical or conservative interventions included a broader range of evidence (including level 2 and 3 studies) and specifically focused on patients with rotator cuff disease. This review found weak evidence to suggest that open and primary surgery were more effective than arthroscopic debridement and revision surgery [39]. However, these conclusions do little to provide guidance on current practice trends as these procedures have different indications and recent techniques were not addressed. No randomized clinical trials have compared mini-open to an all-arthroscopic repair technique.

### A trial is needed now

The wait-list for this procedure ranges from 6 months to 2 years in Canada, indicating a high demand for effective rotator cuff repair procedures. Canadian shoulder surgeons who are active members of JOINTS Canada obtained funding from CIHR to mount a team-planning meeting where we identified and reached a consensus that this research question was the top priority for shoulder surgeons and their patients. The timing of this clinical trial is critical. An RCT mounted too early will have difficulty recruiting a sufficient number of surgeons with the experience required to perform the study interventions. If the trial is delayed until less invasive surgical techniques become the standard of practice, a large group of patients will be exposed to suboptimal care should this practice prove less effective. Further, it will be more difficult to change clinical practice after this shift has occurred. Currently, surgeons are making decisions about abandoning traditional repairs in the search of the ideal minimally invasive procedure. Without the benefit of high-quality evidence to support these decisions, premature selection may expose patients to potentially useless or risky procedures. Certainly, haphazard incorporation of new surgical approaches exposes the health care system to inefficient allocation of its limited resources.

## Methods/Design

### Primary objective of the trial

To compare the effectiveness of all-arthroscopic to mini-open rotator cuff repair to improve the quality of life of patients with a small or medium-sized rotator cuff tear.

### Secondary objectives

While maximizing the patient's quality of life is clearly the primary objective, the direct intent of repairing the defect in the cuff is to restore its integrity and functionality. Previous work has shown that self-report measures are poor indicators of this functionality when measured by strength [40], motion [40], or imaging [19]. Therefore, these are important secondary outcomes. Generic health issues and specific work limitations are important outcomes that are not fully addressed by the WORC. Therefore, our secondary objectives are to compare the impact of all arthroscopic to mini-open rotator cuff repair on work limitations (WL-26) [41]; general health (SF-12) [42]; physical impairments (range of motion and strength) [15,43,44]; cuff integrity (MRI/ultrasound) [45,46]; and surgical complications.

### Tertiary objective

While both the expertise-based and conventional RCT designs are accepted methodologies and will be implemented in this study to minimize potential biases, it is appropriate to evaluate the impact of these designs on the results of the study. Therefore, we will determine whether the design [34] affects: patients' willingness to participate (or enrollment rates), dropout rates, satisfaction with study participation, and protocol violations (including crossovers).

#### Planned trial interventions

This trial compares two different methods of repairing a torn rotator cuff. Patients will undergo either 1) a mini-open repair where the repair is performed though a small incision and the arthroscope can be used to address problems within the joint (as per traditional diagnostic procedures); or 2) an all-arthroscopic procedure where joint techniques and repair are both performed entirely thought the arthroscope. While many surgeons have used arthroscopy for diagnosis and debridement, repair through the arthroscope is substantially different and requires additional training and experience. Thus, these methods are quite distinct to surgeons. JOINTS Canada surgeons have discussed elements of the repair that can be standardized and those that must be left to surgeon preference. A protocol for surgery/rehabilitation has been established for study centres.

a. *Arthroscopic repair *will consist of subacromial decompression, repair of the torn cuff tendon, and debridement of partial (up to 50%) tears of biceps. If an anatomic repair of the cuff is possible, the area between the articular margin and the greater tuberosity will be decorticated to prepare a bleeding surface for reattachment of the tendon. The anchor selection will be based on the surgeon's personal preference. The number of anchors used will be recorded. After completion of suture anchor placement, braided sutures will be passed through the torn tendon as either mattress or simple sutures at the surgeon's discretion. Side-to-side sutures at the apex of the tear will be used as indicated. The type and number of sutures and suture anchors will be recorded

b. *Mini-open Repair *will follow arthroscopic examination of the glenohumeral joint and subacromial decompression. The arthroscope will be removed and the standard mini-open repair will be performed. A transverse or vertical skin incision at the lateral border of the acromion is made. Exposure of the cuff will be achieved by dissection of the deltoid fascia, and split of the deltoid from the level of the acromion distally for 4 cm. The edges of the tear are resected. The bone between the articular margin and the greater tuberosity is decorticated or a bone trough prepared at the surgeon's discretion. Suture anchors or transosseus sutures may be used along with side-to-side sutures. Details of technique will be recorded as above.

### Subjects

#### Inclusion/Exclusion criteria

We will recruit patients with small or medium-sized rotator cuff tears as determined by clinical examination and diagnostic imaging (MRI) prior to surgery. The full-thickness rotator cuff tears of supraspinatus and infraspinatus will be classified into 2 categories based on longest dimension: SMALL = 0–1 cm; MODERATE = 1–3 cm. Definitive measurement of tear size will be made in surgery and used as a covariate in analysis (JOINTS Canada measurement protocol will be used).

#### Pre-operative exclusion criteria

1) Evidence of major joint trauma, infection, avascular necrosis, chronic dislocation, inflammatory or degenerative glenohumeral arthropathy, frozen shoulder, or previous surgery of the affected shoulder,

2) Evidence of significant cuff arthropathy with superior humeral translation and acromial erosion diagnosed by x-ray or other investigations,

3) Major medical illness (life expectancy less then 2 years or unacceptably high operative risk),

4) Unable to speak or read English,

5) Psychiatric illness that precludes informed consent,

6) Unwilling to be followed for 2 years.

#### Intra-operative exclusion criteria

7) Large, massive, or irreparable cuff tears extending into the subscapularis or teres minor which cannot be mobilized to the articular margin or repaired using one or both of the techniques (all-arthroscopic or mini-open),

8) Teres minor or subscapularis tears,

9) Inelastic and immobile tendon which cannot be advanced to articular margin,

10) Co-existing labral pathologies requiring repair with sutures (SLAP II-IV), Bankart lesions requiring repair, partial tears of biceps (more than 60% of thickness) requiring tenodesis or release.

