#### Conventional RCT

Patients will arrive at their surgical consultation where the surgeon will assess patient eligibility during history and physical examination, taking into account diagnostic information provided from pre-consultation MRI. The surgeon will explain the clinical trial and that by agreeing to participate, the patient has a 50:50 chance of receiving either method (mini-open or all-arthroscopic) to repair the torn rotator cuff tendon. The research assistant will obtain informed consent and contact the central randomization computer to obtain patient identification number and treatment assignment.

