#### Expertise-based RCT

Patients will arrive at their surgical consultation where the surgeon will assess patient eligibility as per above. If eligible, the surgeon will explain the clinical trial and that by agreeing to participate, the patient has a 50:50 chance of receiving either method (mini-open or all-arthroscopic) to repair the torn rotator cuff tendon and that another surgeon from the same centre may perform the operation depending on group allocation; the surgeon performing the procedure will have expertise in performing that procedure. The research assistant will obtain informed consent and contact the central randomization computer to obtain patient identification number and surgeon (treatment) assignment. Two of the larger centres (Calgary and London) have some surgeons who qualify for the conventional RCT and others (pairs) for the expertise-based RCT so this factor will also be block randomized at these sites.

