#### Proposed methods for protecting against other sources of bias

##### Control over eligibility violations is under review of the central adjudication committee

The Central Adjudication Committee (CAC), blinded to patient group allocation, will review all operative reports and eligibility forms from all randomized patients to ensure they met eligibility criteria. This committee will consist of the principal investigator, an orthopaedic surgeon, and an epidemiologist. Any patient judged to be ineligible by the CAC, according to information available at the time of randomization, will be omitted from the final analysis and the reason for exclusion recorded. This will be recorded as a minor protocol violation.

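### Patients are randomised at the consultation but can be excluded in theatre by an unblinded surgeon, and the protocol's own rules conflict on whether such patients are excluded, crossovers or analysed

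*Protocol article*

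**What the plan says.** All references are to the protocol article.

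- **Allocation comes first.** Under *Conventional RCT*, the research assistant takes consent at the consultation and is then to "contact the central randomization computer to obtain patient identification number and treatment assignment". Under *Expertise-based RCT*, the call is to "contact the central randomization computer to obtain patient identification number and surgeon (treatment) assignment". There the allocation decides who operates, so it must precede theatre.
- **Exclusions follow in theatre.** *Intra-operative exclusion criteria* lists four. Criterion 7 covers large, massive or irreparable tears that "cannot be mobilized to the articular margin or repaired using one or both of the techniques (all-arthroscopic or mini-open". Criterion 9 is "Inelastic and immobile tendon which cannot be advanced to articular margin". Criteria 8 and 10 are anatomical: tears of particular tendons, and labral, Bankart or biceps lesions that need further treatment.
- **The surgeon knows the arm.** *Control of biases through blinding* accepts that surgeons are not blinded.
- **Adjudication.** A committee described as blinded to allocation "will review all operative reports and eligibility forms from all randomized patients". A patient whom it judges ineligible, "according to information available at the time of randomization, will be omitted from the final analysis".
- **Crossovers.** *Control of contamination and co-intervention* records them as major protocol violations.
- **Comparison.** *Planned analyses* words the pooled comparison by the operation that patients had.
- **Allowance.** *Sample size* adds 15% for withdrawal, loss to follow-up and crossover. Exclusion in theatre is not named.

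**The concern.** An exclusion made after allocation, by someone who knows the allocation, is no longer protected by randomisation. If hard-to-repair shoulders are removed more often in one arm, that arm's remaining patients look better for reasons unrelated to the technique. If those patients are not followed, the analysis cannot recover them later.

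The article recognises this hazard elsewhere. Its review of earlier comparisons faults a study in which patients had mini-open repair after arthroscopic repair had failed technically. It also expects surgeons in the conventional design to depart from assignment in some cases.

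The second problem is definitional. Two analysts reading this article could build different primary populations, because the sections that bear on a patient excluded in theatre give different answers.

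**Working it through.** **1. What happens to a randomised patient who meets one of criteria 7 to 10?**

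| Section | Consequence if followed literally |
|---|---|
| Intra-operative exclusion criteria | The patient is excluded |
| Central adjudication | The patient stays, because an operative finding is not available at randomisation; yet operative reports are read to check eligibility |
| Contamination and co-intervention | If the other technique is used, the patient is a crossover |
| Planned analyses | The patient is counted under the operation received; no place is given to one who had neither repair |
| Sample size | Crossovers are covered by the 15% allowance; theatre exclusions are not mentioned |

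No section separates a tear excluded as not repairable by the assigned technique from one that crosses over.

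**2. Which criteria could depend on the arm?** Criterion 7 names the techniques, and the surgeon observes only the one being attempted. Criterion 9 is a judgement about tendon mobility made during the operation. Criteria 8 and 10 are anatomical, and *Planned trial interventions* has the mini-open repair follow an arthroscopic examination, so both arms get a similar first look.

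**3. The plan's own figures.** Inputs from *Sample size*: SD 450, r = 0.55, difference 142.5, 1.96 and 0.84.

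- n per group = 2 × (1.96 + 0.84)² × 450² × (1 − 0.55²) / 142.5² = 109.07, so 109 is reproduced.
- 2 × 109 × 1.15 = 250.7, so 250 is reproduced.

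**4. Power with further exclusions.** Residual SD = 450 × √(1 − 0.3025) = 375.8. Analysable n per arm = 125 × 0.85 × (1 − x), where x is an assumed exclusion rate equal in both arms. Power = Φ(142.5 / (375.8 × √(2/n)) − 1.96). The last column is 2 × ⌈109 / (0.85 × (1 − x))⌉.

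| x | n per arm | Power | Total N to keep 109 per arm |
|---|---|---|---|
| 0% | 106.2 | 78.9% | 258 |
| 5% | 100.9 | 76.8% | 270 |
| 10% | 95.6 | 74.6% | 286 |
| 15% | 90.3 | 72.2% | 302 |

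The start is 79%, not 80%, because 125 less 15% is 106.25 rather than 109.

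**5. Possible bias.** Assume no true effect and excluded patients whose two-year mean is D points worse than that of retained patients in their arm. The retained mean is then better than the full-arm mean by (exclusion rate × D), so bias = (difference in exclusion rates) × D. Type I error is two-sided, with 109 per arm before exclusion. All rates and values of D are assumptions.

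| Excluded, arm A v arm B | D | Bias (points) | Share of 142.5 | Type I error |
|---|---|---|---|---|
| 2% v 2% | any, equal in both arms | 0 | 0% | 5.0% |
| 5% v 2% | 225 to 650 | 7 to 20 | 5% to 14% | 5.2% to 6.6% |
| 10% v 2% | 225 to 650 | 18 to 52 | 13% to 36% | 6.4% to 16.7% |
| 10% v 2% | 450 | 36 | 25% | 10.5% |

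**The case against.** The strongest reply is that criterion 7 is narrower than its wording about techniques suggests. Its subject is large, massive or irreparable tears extending into subscapularis or teres minor. Criterion 8 excludes tears of those tendons whatever the technique, and *Inclusion/Exclusion criteria* limits the trial to tears of up to 3 cm. A reader might infer that a tear which defeats the arthroscopic attempt is dropped in one arm while the same tear is repaired and kept in the other. The documents do not support that: most tears under criterion 7 should be out in either arm. Read literally, a requirement of repairability by both techniques is even neutral between arms. What stands is that the surgeon sees only the assigned technique, knows which it is, and also judges criterion 9.

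A reader might also infer that the committee itself creates exclusions that differ by arm. It need not. Its limit to information available at randomisation is a safeguard and, if followed, prevents removal on operative findings. Operative reports ordinarily reveal the repair, but masked reports may be described in the full protocol, which is not shown. The conflict between that limit and the intra-operative list remains.

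Finally, a reader might take "The wait-list for this procedure ranges from 6 months to 2 years in Canada" as the gap between allocation and surgery. The article does not say where that wait starts, so a long gap is not established.

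**Conclusion.** The concern holds as a conflict in the rules with a possible route to bias. Allocation precedes theatre, an unblinded surgeon applies further exclusions there, at least criteria 7 and 9 involve judgement that can differ by arm, and the sections disagree on the status of the patients affected.

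Bias is possible but not demonstrated. The documents give no exclusion rate, so neither its size nor its direction is known. Under the assumed 10% v 2% with D = 450 it would be 36 points and a type I error of about 10.5%. Under 5% v 2% it is small, and with equal rates of similar patients it is nil. The power loss, from about 79% to 77% or 75%, assumes a further 5% to 10% excluded on top of 15% other losses.

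**What to change.** Reconcile *Intra-operative exclusion criteria*, the central adjudication section, *Control of contamination and co-intervention* and *Planned analyses*:

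1. State that every randomised patient, including one who meets an intra-operative criterion, is followed to two years and kept in the primary analysis in the arm assigned.
2. Add a sensitivity analysis without these patients, and report their number and reasons by arm.
3. If any are nevertheless to be omitted, limit this to findings that cannot depend on the arm, recorded at the arthroscopic examination before repair and adjudicated from material with the repair section masked. Then restate the expected evaluable number and the power.

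The cost is wording, follow-up of a few patients who did not have the planned repair, and slight dilution of the effect. Criteria 8 and 10 need no rewording for this purpose, and no clinical eligibility rule has to change. Releasing the allocation later in the conventional design is optional. It is an operational redesign, and it would not solve the problem in the expertise-based design, where allocation must precede theatre.
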